##### Ectopic fat

Excess adiposity is associated with an accumulation of fat in multiple organs and tissues. Fat accumulation in the liver and pancreas promotes a pro-inflammatory state that may increase the risk of insulin resistance and T2D. Likewise, ectopic fat accumulation seems to be an important predictor of the onset of T2D in adolescents [49]. Insulin sensitivity was 55% lower in adolescents with hepatic steatosis compared to those without fatty liver disease. Few studies have examined fat accumulation in the pancreas and its relationship with insulin resistance and T2D. Pancreatic steatosis seems to be associated with prediabetes in children increasing the risk of T2D and cardiovascular disease [50–52]. Nevertheless, other studies reported no significant associations of pancreatic fat and β-cell dysfunction [53]. There are no previous studies examining the effect of either a lifestyle modification program or an exercise program on pancreatic fat. Hepatic and pancreatic fat will be measured by magnetic resonance imaging using a 1.5-T system (MAGNETOM Avanto, Siemens Healthcare, Erlangen, Germany) equipped with a phased-array surface coil and a spine array coil.

##### Cardiorespiratory fitness

Cardiorespiratory fitness is an independent predictor of T2D in adults [54]. In youths, there is evidence indicating a negative association between cardiorespiratory fitness and insulin resistance [55]. Moreover, previous reports suggested that that the relationship between cardiorespiratory fitness and T2D may be mediated by an increased susceptibility to fat deposition in liver and pancreas, increasing thereby insulin resistance [49, 56]. Cardiorespiratory fitness will be assessed by two different tests as published elsewhere [45]: (1) the 20-m shuttle run test [57]. We will use the equation reported by Léger et al. [57] to estimate the maximum oxygen consumption (VO_2max_, ml/kg/min) from the 20-m shuttle run test scores and (2) direct cardiopulmonary exercise progressive incremental treadmill test using the modified American College of Sports Medicine protocol with respiratory gas analysis to exhaustion [58].

##### Carotid intima-media thickness

Early changes of atherosclerosis can be detected assessing carotid intima-media thickness (cIMT). In adolescents with T2D, Shah et al. reported that every 1% increase in hemoglobin A1c (HbA1c) or each year increase of the duration of the disease was associated with 30% higher cIMT [59]. In children with obesity, cIMT was higher in those with prediabetes than in their counterparts with normal glucose tolerance [60]. cIMT will be measured by ultrasound (General Electric, Logic S8 model) according to international recommendations. All studies will be done following a standardized scanning protocol for the right and left common carotid arteries. The common carotid artery bulb will be identified and the segments of common carotid arteries 1–2 cm proximal to the bulb region will be scanned. During the end of the diastole cIMT will be measured in both carotids four times and mean cIMT and maximal cIMT will be calculated. Also in telediastole, two sides of maximal diameter of the common carotid, bulb and internal carotid will be measured.

##### Inflammation and biochemical cardiovascular disease risk factors

The obesity-associated chronic inflammatory process participates in the onset of T2D, although the underlying mechanisms are not well understood [61, 62]. Several studies have suggested that inflammatory cytokines may influence insulin sensitivity, both directly and also indirectly mediated, by adipokines, such as leptin and adiponectin, and hepatokines such as fetuin-A and fibroblast-21 growth factor (FGF-21) [62–65]. Biochemical variables will be measured from venous fasting blood samples obtained from each child by experienced nurses. Blood samples will be immediately centrifuged, aliquoted and stored at −80 °C or below. This permits the measurement of a full set of cardiovascular markers including lipid profile (total cholesterol, HDL- and LDL-cholesterol and triglycerides), glucose, insulin, HbA1c, cytokines (e.g., tumor necrosis factor alpha and interleukin (IL)-6) adipokines (e.g., leptin and adiponectin), hepatokines (fetuin-A and FGF-21), liver enzymes (alanine aminotransferase, aspartate aminotransferase and gamma-glutamyl transferase), C-reactive protein and uric acid. ELISA kits, Western blots and High Performance Liquid Chromatography-Mass Spectroscopy will be used to perform these analyses.

##### Physical activity, sedentary behavior, dietary assessment and sleep

We will assess all these lifestyle behaviors both at the beginning and the end of the intervention. Children will wear an accelerometer on the non-dominant wrist (ActiSleep, Actigraph, Pensacola, FL, USA) for seven consecutive days for 24 h to record physical activity intensity levels and patterns, as well as sleeping habits and participants will also complete a diary log. Sedentary behaviors, such as watching TV, playing computer games, playing video games or phone games and surfing the Internet, will be self-reported by the children using validated questionnaires [66]. Dietary intake will be evaluated by two non-consecutive 24-h recalls within a period of 7 days by nutritionists and a self-reported semi-quantitative food frequency questionnaire.

### Outcome measures for the second objective

Recently, miRNAs have emerged as key regulators of gene expression. T2D is associated with changes in the level of several miRNAs in pancreatic β-cells as well as in tissues such as liver, skeletal muscle or adipose tissue [67, 68]. Moreover, miRNA expression seems to participate in the regulation of the IRS mediated by the regulation of inflammatory processes [39]. As has been mentioned in previous sections, the second primary aim of the present work is to characterize the miRNA species present in circulating white blood cells and exosomes, before and after the intervention program is applied. Our initial hypothesis is that the application of this program will have a direct impact on the miRNA species present in blood cells and exosomes, and that these changes will influence the physiological effects elicited by the exercise program.

#### Extraction and isolation of miRNAs from white blood cells and plasma

Exosomes will be obtained from 1 ml of plasma using the Total Exosome Isolation Kit (Thermo Fisher Scientific) following manufacturer’s protocols. RNA molecules will be isolated from white blood cells (buffy coat) and exosomal fractions using Qiagen miRNeasy kit (Qiagen, Hilden, Germany) according to the manufacturer’s instructions. Once isolated, RNA will be quantified using a fluorimetric method.

#### Analysis and validation of miRNAs

Species of miRNA present on samples of individual subjects, before and after the intervention program, will be analyzed using RNA-seq methodology on Illumina’s MiSeq Next Generation Sequencing system. This workflow allows one to fully characterize the miRNA profile present in the samples analyzed (exosomes and white blood cells) and to quantify the expression levels of different miRNA species. In this sense, effects of the intervention program on the miRNA profile and on expression level of specific species can be inferred. Briefly, Illumina’s TruSeq Small RNA Sample preparation kit will be used to generate sequencing libraries, from 1 μg of total RNA isolated from previous samples (either exosomes or white blood cells). Only 145 to 160 bp libraries will be selected for sequencing, as they include miRNA species (22–30 bp plus adapters). Sequencing reactions will be performed on Illumina’s MiSeq Reagent Kit V3, which supports to multiplex up to 10 samples on a single run, and single reads of 50 nt in length. Analysis of results, FASTQ files generation and sequence alignment will be performed using specific software packages (MiSeq Reporter, Bowtie, SAMtools, DESeq2 and miRDeep).

### Confounding variables

#### Puberty stage

At baseline, the pediatrician will evaluate Tanner staging by direct-examination breast palpation in girls and testicular measurement by orchidometer in boys.

#### Sociodemographic variables

Information about socioeconomic status, demographic characteristics and family medical history of obesity, diabetes, dyslipidemia and hypertension will be collected. Socioeconomic status will be evaluated using The Family Affluence Scale [69] and parental education level and parental occupation. As demographic characteristics, date of birth, sex, ethnicity and family structure will be recorded.

### Assessment of side effects

All adverse effects or health problems attributable to the testing or exercise sessions will be recorded.

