#### Randomization

Eligible participants will be randomly assigned after completing the baseline measurements to either the control group or the or exercise group (Fig. 2). Randomization of the participants into the control or exercise group will be done using Statistical Package for Social Sciences (IBM SPSS Statistics for Windows, version 21, Armonk, NY, USA) by an independent researcher. Assessment staff will be blinded to participant randomization assignment. Participants and their parents or guardians will be explicitly informed of the group to which they will be assigned, as well as of the study hypotheses. As exercise is potentially beneficial for the health of the children recruited in this trial, the waiting list control group strategy will be used, which means that the control group will receive the same exercise program when the post-intervention evaluations are finished.

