#### Family based healthy lifestyle education and psycho-educational intervention

Families in the control and the exercise groups will attend both the healthy lifestyle education and psycho-education program once every 2 weeks (11 sessions over 22 weeks) for 90 min (45 min in the healthy lifestyle education program and 45 min in the psycho-educational intervention). The design of the programs has been published elsewhere [45]. Briefly, the sessions of the healthy lifestyle education and psycho-educational interventions will be developed simultaneously and delivered to both parents (or caregivers) and children, separately.

The family based healthy lifestyle education program will be conducted by experienced nutritionists. The aim of the program will be in promoting changes in lifestyle behaviors strongly associated to obesity and T2D risk: promoting healthy dietary habits (reducing the intake of sugar, sugar-sweetened beverages and energy-dense foods, enhancing the daily consumption of fruits and vegetables, promoting breakfast and eating five meals/day), increasing regular physical activity levels, reducing time spent in sedentary behaviors and promoting sleep hygiene and adequate sleep duration.

The aims of the psycho-educational program will be to provide parental skills to optimize the family environment in order to make positive changes in their lifestyles and to learn assertive communication skills. The program will also provide skills to children for managing the emotions and feelings that they are experiencing and to improve their self-esteem and psychological wellbeing.

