#### Exercise training intervention

The exercise group will do exercise 3 days/week, 90 min per session, over a 22-week period. The program will be open to the families 5 days per week to choose a total of 3 days/week. Sessions will be designed and supervised by exercise specialists. The design of the exercise program has been published elsewhere [45]. Briefly, the program consists of cardiovascular endurance (60 min) and muscle strength exercises (10 min). The sessions also include 10 min of warm-up period, 5 min for giving instructions and 5 min of cool-down period at the end, consisting mainly of stretching exercises. Moderate to vigorous intensity aerobic workout is the main part of the exercise session (60 min) and consists of games, circuits and start-and-stop activities. The emphasis of the program is on intensity doing special emphasis on high intensity activities (above 75% of maximal heart rate (HRmax) obtained from either the cardiopulmonary exercise test in the laboratory or the 20-m shuttle run test) and enjoyment. Participants will wear a heart rate monitor (Polar RS300X) during the exercise sessions to ensure achievement of the target heart rate zone. Heart rate monitors will be programmed according to individual percentage of HRmax as follows: (1) very light intensity: from 50 to 57% of HRmax, (2) light intensity: from >57 to 64% of HRmax, (3) moderate intensity, from >64 to 76% HRmax, (4) high intensity or vigorous: from >76 to 96% HRmax and (5) maximal intensity: > 96% of HRmax.

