### Outcome measures for the first objective

IRS and the risk of T2D is characterized by excess adiposity, low levels of insulin sensitivity, dyslipidemia and hypertension. In the current project, the primary outcome is insulin resistance. Secondary outcome variables include total, abdominal and visceral adiposity, ectopic fat (hepatic and pancreatic fat), cardiorespiratory fitness, cardiovascular disease risk factors and inflammation markers, hepatokines and adipokines (Table 2). Primary and secondary outcomes will be evaluated at baseline and repeated after 22 weeks of intervention (Fig. 2). Post-intervention measurements will be scheduled within 3 days following the last healthy lifestyle program session or exercise session in the control or in the exercise group, respectively.

**Table 2 Tab2:** Summary of the methodology of primary and secondary outcome measurements and potential confounders in the PREvention of DIabetes in KIDs (PREDIKID) study

Measure	Methodology
Primary outcomes	
Insulin resistance	Homeostatic model assessment (HOMA), biochemical analyses
Expression of miRNA in circulating exosomes and white blood cells	RNA-seq methodology
Secondary outcomes	
Physical measures	
Body mass (kg)	Scale
Height (cm)	Stadiometer
Waist circumference (cm)	Non-elastic tape
Blood pressure (mmHg)	Oscillometric monitor device
Body fat (%)	Dual X-ray absorptiometry
Abdominal adiposity (g)	Dual X-ray absorptiometry
Visceral abdominal adiposity (cm^2^)	Magnetic resonance imaging
Hepatic fat (%)	Magnetic resonance imaging
Pancreatic fat (%)	Magnetic resonance imaging
Carotid intima medial thickness (mm)	Doppler ultrasonography
Biochemical measures	
Glucose (mg/dL)	Enzymatic spectrophotometry
Insulin, leptin, adiponectine, fetuin-A, FGF21	Enzyme-Linked Immunosorbent Assay
Hemoglobin A1c	Enzymatic tests
Total cholesterol, HDL- and LDL-cholesterol (mg/dL)	Enzymatic spectrophotometry
Triglycerides (mg/dL)	Enzymatic spectrophotometry
Alanine aminotransferase (U/L)	Enzymatic tests
Aspartate aminotransferase (U/L)	Enzymatic tests
Gamma glutamyl transferase (U/L)	Enzymatic tests
C-reactive protein (g/dL)	Enzyme immunoassay
TSH, T3, T4	Radioimmunoassay
Uric acid (mg/dL)	Enzymatic spectrophotometry
Urea, bilirubin	Enzymatic spectrophotometry
Cardiorespiratory fitness	20-m shuttle run test Cardiopulmonary exercise test
Dietary assessment	24-h recalls and food frequency questionnaires
Physical activity assessment	Accelerometry and questionnaires

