### Data management and monitoring

Participants’ data will be identified only by a study number (starting with 001) and only the principal investigator and study coordinator will have access to identifiers that can link the data to the individual participant. Participants who drop out will be noted and their reasons documented. Data will be entered and stored on a standalone computer into excel and SPSS data files, and the information will be password protected. We will assure the quality of data entry by random checking of the data entered. Study data is only accessible by the researchers involved in the trial, and only the principal investigator and investigators in the project will have access to the data for analysis. The investigators will monitor that the informed consent process is conducted appropriately and that informed consent was obtained prior to proceeding with any study procedures. Only participants who meet study eligibility criteria will be enrolled. Data will be kept for 10 years after the research is completed and all data (electronic and hard copy) will be destroyed after the storage period. There is no data monitoring committee due to the characteristics of the current study.

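### The stated adverse-event rule admits only events attributable to testing or exercise sessions, so capture differs by arm and all-cause events cannot be compared

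*Protocol article*

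**What the plan says.** The Assessment of side effects section is a single sentence: "All adverse effects or health problems attributable to the testing or exercise sessions will be recorded". The design around it is as follows.

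- **Exercise arm** (Exercise training intervention): "The exercise group will do exercise 3 days/week, 90 min per session, over a 22-week period".
- **Control arm** (Randomization): "the control group will receive the same exercise program when the post-intervention evaluations are finished". Controls therefore have no exercise sessions during the comparison.
- **Contact common to both arms**: "Families in the control and the exercise groups will attend both the healthy lifestyle education and psycho-education program once every 2 weeks", given as 11 sessions (section Family based healthy lifestyle education and psycho-educational intervention). The recording rule does not name these sessions.
- **Testing** (Outcome measures for the first objective): "Primary and secondary outcomes will be evaluated at baseline and repeated after 22 weeks of intervention". Under Randomization, "Eligible participants will be randomly assigned after completing the baseline measurements", so baseline testing comes before allocation.
- **Other capture** (Data management and monitoring): dropouts and their reasons are documented, with no restriction by arm. The same section adds: "There is no data monitoring committee due to the characteristics of the current study".

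Neither the outcome list nor the Data analyses plan contains a safety outcome or a comparison of adverse events between arms.

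**The concern.** The rule asks whether an event is attributable before it is written down, and one of its two qualifying sources, the exercise session, exists in only one arm. The same illness or injury could therefore be recorded in an exercise child and go unrecorded in a control. There would be no background rate against which to set the exercise-arm count, and a problem that nobody connected with a session could go unrecorded in either arm.

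What is at stake is the reporting of harms from a programme that emphasises high-intensity work in overweight or obese children aged 8 to 12, and that the Discussion puts forward as a possible preventive model. Events not collected during the trial cannot be recovered by any later analysis plan.

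**Working it through.** **1. The plan's own figures.** The article states no figure for adverse events. The only stated figure used here is the arm size of 42, so I checked that it is sound. With d = 0.7, two-sided α = 0.05 (sidedness is not stated, so this is assumed) and 80% power, n = 2 × (1.96 + 0.84)² / 0.7² = 32, or 33 per group from unrounded quantiles rounded up. The t-test version gives 33.02, rounded up to the stated 34. For 20% loss, 34 / 0.8 = 42.5 (43) and 34 × 1.2 = 40.8 (41). The stated 42 lies between these. Nothing in this point changes it.

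**2. Sources of a recordable event between randomisation and the end of the comparison.**

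| Source | Exercise arm | Control arm | Named in the rule? |
|---|---|---|---|
| Exercise sessions per child, as scheduled | 3 × 22 = 66 (66 × 1.5 h = 99 h) | 0 | Yes |
| Post-intervention test battery | 1 | 1 | Yes |
| Education and psycho-education sessions | 11 | 11 | No |
| Dropout reasons | Documented | Documented | No (recorded under data management) |

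Baseline testing is also recordable, but it precedes allocation and cannot inform a comparison between arms. Control children's later exercise sessions fall after the post-intervention evaluations, so they lie outside the comparison too.

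Across 42 children the exercise arm has 66 × 42 = 2,772 scheduled child-sessions. That count assumes full attendance and no dropout. It shows the asymmetry in opportunity and does not measure bias.

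**3. Illustration on assumed rates.** The documents give no event risks, so I assumed the following:

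- the true any-cause risk p is the same in both arms, counted as children with an event;
- a share f of exercise-arm events is judged session-related;
- testing-related events are set aside, so the control count is 0.

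Expected recorded events in the exercise arm are 42 × p × f. The last column is the probability that Fisher's exact test of that count against 0 of 42 gives p ≤ 0.05.

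| p | f | Expected recorded, exercise arm | Recorded, control arm | Probability of a false difference |
|---|---|---|---|---|
| 20% | 0.25 | 42 × 0.20 × 0.25 = 2.1 | 0 | 0.02 |
| 20% | 0.50 | 42 × 0.20 × 0.50 = 4.2 | 0 | 0.24 |
| 20% | 0.75 | 42 × 0.20 × 0.75 = 6.3 | 0 | 0.62 |

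Over p from 10% to 40% and f from 0.25 to 0.75, the probability runs from 0.001 to 0.995. If all events were recorded in the same way in both arms, each arm would expect 42 × 0.20 = 8.4 at p = 20% (4.2 to 16.8 over 10% to 40%).

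The range is too wide to say anything about the size of the distortion in this trial, and the protocol plans no such test. The illustration shows only that equal true risks can yield unequal recorded counts under the stated rule.

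**The case against.** The case on the other side is substantial, and much of it stands.

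- **The word only is an inference.** The sentence says what will be recorded and does not say that other events will be ignored. A journal article condenses a fuller protocol, which may provide for more. That limits certainty. But the sentence is not silent on scope: it states a restrictive condition, and nothing else shown relaxes it.
- **No planned analysis is defeated.** Safety is not an aim or a listed outcome, and no between-arm comparison of events is promised. This stands, so the point is about a poorly chosen rule and not about an inconsistency.
- **Controls are not without capture.** Testing-related events count in both arms, and the post-intervention battery includes a shuttle run and a treadmill test to exhaustion. Dropout reasons are documented as well. This stands.
- **Some safety information survives.** Attendance at exercise sessions is recorded, so session-related events per attended session can be estimated without a control group. This stands.
- **Delayed problems are not excluded.** The rule covers problems attributable to a session whenever they come to light, and exercise children are scheduled three times a week, which gives frequent opportunity to report. A later problem is lost only if nobody makes the link.

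A reader might also infer that staff who know the allocation filter the events. The article does not say who judges attribution. Families know their group and session supervisors necessarily do, but assessment staff are blinded. Nor does the lack of a monitoring committee bear on the point, since a committee would not change which events are recorded.

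**Conclusion.** The point holds in a limited form. Under the rule as written, event capture after randomisation differs by arm: exercise sessions and post-intervention testing in one, post-intervention testing alone in the other, with dropout reasons in both. All-cause events therefore cannot be compared between arms, and harms not linked to a session may go unrecorded.

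This rests on reading the sentence as the full recording rule, which a longer protocol could alter. The size of any distortion is unknown, because the documents give neither event rates nor the share that would be judged attributable.

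Two stronger readings are tempting and should not be drawn. One is that the exercise arm must show more events by construction. An excess is to be expected, but its occurrence depends on rates the documents do not give. The other is that no conclusion about safety is possible. Events recognised as session-related remain describable, and what is lost is the all-cause contrast. The HOMA analysis, the sample size and the efficacy conclusions are untouched. This is a cheap improvement worth making.

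**What to change.** Amend the Assessment of side effects section so that all adverse events and injuries, whatever the suspected cause, are recorded in both arms from randomisation to the week-22 visit. Ask the same short question of both arms at each of the 11 fortnightly education sessions and again at week 22. Record relatedness to testing or exercise as a separate field, after the event has been entered. Tabulate all-cause and related events by arm. It would help to mark events that came to light at exercise sessions and not through the common question, because the extra contact in the exercise arm would otherwise bring back unequal capture.

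If the fuller protocol already provides for this, one sentence saying so is enough. The cost is one added question, for example on the existing attendance record, and a little more data entry, with some minor unrelated events recorded. No efficacy analysis or sample-size figure changes. Recruitment began in March 2017, so the date of the change should be noted and children followed under the present rule identified.
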